## Abstract

**Background:**

Insertion of an external ventricular drain (EVD) is a first-line treatment of acute hydrocephalus caused by aneurysmal subarachnoid haemorrhage (aSAH). Once the patient is clinically stable, the EVD is either removed or replaced by a permanent internal shunt. The optimal strategy for cessation of the EVD is unknown. Prompt closure carries a risk of acute hydrocephalus or redundant shunt implantations, whereas gradual weaning may increase the risk of EVD-related infections.

**Methods:**

DRAIN (*Danish RAndomised Trial of External Ventricular Drainage Cessation IN Aneurysmal Subarachnoid Haemorrhage*) is an international multicentre randomised clinical trial comparing prompt closure versus gradual weaning of the EVD after aSAH. The primary outcome is a composite of VP-shunt implantation, all-cause mortality, or EVD-related infection. Secondary outcomes are serious adverse events excluding mortality and health-related quality of life (EQ-5D-5L). Exploratory outcomes are modified Rankin Scale, Fatigue Severity Scale, Glasgow Outcome Scale Extended, and length of stay in the neurointensive care unit and hospital. Outcome assessment will be performed 6 months after ictus. Based on the sample size calculation (event proportion 80% in the gradual weaning group, relative risk reduction 20%, alpha 5%, power 80%), 122 participants are required in each intervention group. Outcome assessment for the primary outcome, statistical analyses, and conclusion drawing will be blinded. Two independent statistical analyses and reports will be tracked using a version control system, and both will be published. Based on the final statistical report, the blinded steering group will formulate two abstracts.

**Conclusion:**

We present a pre-defined statistical analysis plan for the randomised DRAIN trial, which limits bias, p-hacking, and data-driven interpretations. This statistical analysis plan is accompanied by tables with simulated data, which increases transparency and reproducibility.

**Trial registration:**

ClinicalTrials.gov identifier: NCT03948256. Registered on May 13, 2019.

## Introduction

Acute hydrocephalus occurs as a common and severe complication and is treated with an external ventricular drain (EVD) in the acute phase [1–3]. Up to 37% of patients with an EVD develop chronic hydrocephalus requiring a ventriculo-peritoneal (VP) shunt [4]. The optimal strategy for EVD discontinuation in terms of safety minimising the need for a VP shunt is unknown. Two different strategies to end EVD treatment are commonly used: prompt closure or gradual weaning. Gradual weaning implies a stepwise increase of outflow resistance over days [5, 6]. This has been suggested to allow time for reestablishment of normal cerebrospinal fluid (CSF) circulation, minimise the risk of dramatic changes in intracranial pressure (ICP), and potentially protect brain tissue. However, prolonged EVD treatment increases the risk of serious and potentially fatal infection [7]. Conversely, prompt closure of the EVD may minimise the time with an EVD and thereby the risk of infection, which again may shorten the hospital length of stay with the possibility to start rehabilitation earlier [8]. The main drawback of this strategy is the risk of inducing increased ICP and acute hydrocephalus.

It is currently unknown whether these two main strategies for EVD discontinuation differ in terms of functional outcome, risk of VP-shunt placement, or risk of EVD-related infection. The DRAIN randomised clinical trial was initiated with the objective to directly compare the benefits and harms of these two regimens of EVD cessation after aSAH. This paper describes the plan for the statistical analyses of the clinical outcomes.

## Methods

The DRAIN trial is an international multi-centre, 1:1 randomised, parallel-group, superiority clinical trial investigating gradual weaning versus prompt closure of EVD in patients with hydrocephalus following aSAH. The trial was registered at ClinicalTrials.gov with identifier no. NCT03948256 before inclusion of the first patient. The detailed trial protocol has been published elsewhere [9]. In short, all adult patients admitted to one of the participating neurosurgical departments with a diagnosis of aSAH and a need for EVD placement will be screened for enrolment. Each trial participant is allocated a unique patient trial number. Following successful treatment of the ruptured aneurysm, in eligible participants, the EVD resistance will be set to 10 cm H_2_O to ensure a uniform drainage production prior to intervention. An increase of drainage resistance to 15 cm H_2_O may be done if a high drainage volume is the only factor that keeps the patient from being randomised. When the participant fulfils all the inclusion criteria and none of the exclusion criteria, they will be randomised, and the allocated intervention (gradual weaning versus prompt closure) will be initiated immediately hereafter. Participants must fulfil the inclusion criteria within 18 days after ictus in order to be included in the trial. This statistical analysis plan follows the guidelines for statistical analysis plans [10].

Inclusion criteria:

> 18 years of ageDiagnosis of aneurysmal subarachnoid haemorrhage (aSAH)External ventricular drain (EVD) for > 6 daysaDrain output of < 220 mL/day at a resistance of 10 or 15 cm H2OStable or improving Glasgow Coma Scale (GCS) > 9 during the last 24 hSigned informed consent (from patient or next-of-kin)

Exclusion criteria:

Severe pre-existing (physical or mental) disability or severe co-morbidity that would lead to poor outcome even if the patient made a full recovery from the aSAHLife expectancy shorter than 48 hours after admission

### Randomisation and blinding

Eligible participants are randomised 1:1 according to a computer-generated allocation table generated by the data manager at the Copenhagen Trial Unit using concealed and varying block sizes and the following stratification variables:

Modified Fisher grade < 3 compared to > 3,Age in years < 60 years compared to > 60 years, andSite

The allocation sequence list will be unknown to the investigators to allow immediate and concealed allocation of trial participants.

Due to the nature of the interventions, blinding of participants and clinicians is not possible. Investigators, statisticians, and conclusion drawers will be blinded to the allocation during analysis and interpretation of the results. Blinded outcome assessors will carry out assessment of the primary composite outcome. Unblinded trial investigators will assess the remaining outcomes. The outcomes are not evaluated by blinded investigators, which may introduce bias. However, the primary outcome is an objective assessment not susceptible to bias.

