### Continuous outcomes

Continuous outcomes will be presented as means and 95% confidence intervals for each group, with an annotation in the tables of the percentage of missing data per group. We will use mixed-effects linear regression model adjusted with stratification variables as fixed effect and site as random effects [23].

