### Ordinal outcomes

Ordinal outcomes will be presented as proportions for each level and for simplicity also dichotomized into favourable and unfavourable. For mRS, 0–2 is favourable, and 3–6 is unfavourable [13, 14]; for GOSE, > 5 is favourable, and ≤ 5 is unfavourable [15]. Ordinal outcomes will be analysed using ordinal logistic regression with stratification variables as fixed effect and site as random effects [27, 28]. The results will be presented as relative risks (RRs) and confidence intervals for improving one level on the ordinal outcome [29].

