### Dichotomous outcomes

Dichotomous outcomes will be presented as proportions for each group with an annotation in the tables of the percentage of missing data per group. Dichotomous outcomes will be analysed using mixed-effects logistic regression with stratification variables as fixed effect and site as random effects. We will estimate the marginal effects to obtain RRs and confidence intervals of the RRs (based on ‘nlcom’ from Stata (StataCorp LLC, Texas, USA)) or G-computation in R. We have chosen to—as a primary analysis—investigate our count outcomes without dichotomisation. Inappropriate dichotomisation—even though widely used—results in lower power and possibly also faulty results [28, 30, 31].

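### Outcome regressions adjust for age only as below or above 60, although age in years is collected: a valid choice with a small, avoidable loss of precision

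*SAP article*

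**What the plan says.** Under Randomisation and blinding, the stratification variables are modified Fisher grade, site, and "Age in years < 60 years compared to > 60 years".

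The three model sections under Statistical analysis carry these variables into the outcome models:

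- Continuous outcomes: "We will use mixed-effects linear regression model adjusted with stratification variables as fixed effect and site as random effects".
- Ordinal outcomes: "Ordinal outcomes will be analysed using ordinal logistic regression with stratification variables as fixed effect and site as random effects".
- Dichotomous outcomes, which covers the primary composite: "Dichotomous outcomes will be analysed using mixed-effects logistic regression with stratification variables as fixed effect and site as random effects".

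No section enters age in years into an outcome model. The only other covariate set named is none at all: the unadjusted, non-imputed analysis under Handling of missing data. The baseline table (Table 2) has a row for age as mean and SD, so the exact value is recorded. Count outcomes use the van Elteren test, which is not a regression and needs strata.

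**The concern.** Randomisation needs categories; a regression model does not. The trial judged age prognostic enough to stratify on, yet the models see only which side of 60 a participant falls. Any relation between age and outcome within each half stays in the residual variation, although the data to remove it are already in hand.

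What is at stake is precision, not validity. Precision still has some value here. The primary outcome has no spare power at 122 per group, and the composite is set to missing when one component is missing. Trial status reports 243 participants already randomised, so within the planned sample any further precision has to come from the analysis.

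**Working it through.** **1. The plan's own figures.** For 80% versus 64% (20% relative reduction), two-sided alpha 0.05 and power 80%:

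- Arcsine form: h = 2·arcsin(√0.80) − 2·arcsin(√0.64) = 0.360. Then n = 2(1.960 + 0.842)²/h² = 121.3, so 122 per group, as stated.
- The pooled normal formula gives 123. Power at 122 per group is 79.9%.
- EQ VAS (difference 11, SD 26.2, 122 per group): 90.6%, against the stated 90%.

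Neither figure takes credit for covariates, so the stated sample size is not affected by this point.

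**2. Share of age's explained variance kept by the split.** The document gives no usable age distribution: Table 2 is simulated, and its SDs of 0.90 and 0.50 cannot be real. Assume normal age and a linear effect. A cut at 60 keeps φ(z)²/[p(1−p)], with z = (60 − mean)/SD and p = Φ(z).

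- Mean 58, SD 12: z = 0.167, φ = 0.393, p = 0.566. Share = 0.1548/0.2456 = 0.63, so 37% is lost.
- Means 57.8 to 59.1, SD 8 to 14: 36% to 38% lost.
- Means 55 to 62, same SDs: 36% to 45% lost.
- Uniform age cut at its median: 25% lost.

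**3. EQ VAS and FSS.** With assumed correlation r between age and outcome, the variance ratio (continuous age over split) is (1 − r²)/(1 − 0.63r²).

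| Assumed r | Ratio | Variance saved | Equivalent of 244 participants |
|---|---|---|---|
| 0.2 | 0.960/0.975 = 0.985 | 1.5% | about 4 |
| 0.3 | 0.910/0.943 = 0.965 | 3.5% | about 9 |
| 0.4 | 0.840/0.899 = 0.934 | 6.6% | about 16 |

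EQ VAS power uses SD 26.2·√(1 − R²) for continuous age and 26.2·√(1 − 0.637R²) for the split (0.637 is the share kept by a cut at the median):

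| Assumed age R² | Split | Continuous |
|---|---|---|
| 2% | 91.0% | 91.2% |
| 5% | 91.5% | 92.0% |
| 10% | 92.4% | 93.3% |
| 20% | 94.0% | 95.6% |

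**4. Primary outcome.** Two simulations were run with 122 per group, leaving out site and modified Fisher grade.

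*Power, continuous age in place of the split (4,000 trials per setting).*

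| Assumed OR per SD of age | Split | Continuous |
|---|---|---|
| 1.0 | 79.8% | 79.6% |
| 1.25 | 78.7% | 78.9% |
| 1.5 | 80.6% | 81.2% |
| 2.0 | 81.6% | 82.7% |

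The first row, where age has no effect, shows that differences of 0.2 points are within simulation noise.

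*Variance, stratum plus continuous age against stratum alone (6,000 trials).* The ratio is 0.994 at an assumed log OR of 0.3 per decade and 0.971 at 0.5 per decade. Blocks of 500 trials varied with SD about 0.010 and 0.017, so over 12 blocks the standard errors are about 0.010/√12 = 0.003 and 0.017/√12 = 0.005. The saving equals 244 × 0.006 ≈ 1.5 and 244 × 0.029 ≈ 7 participants.

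To turn this into power, start from 79.9%, a standardised effect of about 1.960 + 0.837 = 2.797. Then 2.797/√0.994 = 2.805 gives 80.1%, and 2.797/√0.971 = 2.838 gives 81.0%. The gain is about 0.2 to 1.1 points, in line with the power simulation.

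**The case against.** The strongest reply is that nothing here is wrong. Adjusting for the strata as randomised is accepted practice and gives a valid comparison. That stands: a reader who inferred bias or an invalid test would go beyond what the plan supports.

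A reader might also infer that the plan contradicts itself, because the Dichotomous outcomes section says "Inappropriate dichotomisation—even though widely used—results in lower power and possibly also faulty results". It does not. That sentence explains the choice to "investigate our count outcomes without dichotomisation"; it speaks of outcomes and says nothing about covariates.

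A third tempting reading is that about a third of the trial's precision is lost. The figure is a share of age's own linear contribution, under assumptions on distribution and linearity that the document does not supply.

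It would also be too broad to say that every regression in the article uses the age split. The point covers the trial outcome models. The regression for the first embedded study in Table 4 lists drain output and site and names no age term.

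It is fair, too, that the larger gains fall where they matter least. EQ VAS and FSS already have stated power of 90% and 100% and are labelled hypothesis generating. mRS and GOSE are exploratory, and no figure is offered for them.

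The last objection is that strata need no linearity assumption and that a linear age effect on a composite of shunt, death and infection is unproven. This is largely met by keeping the stratum beside the continuous term. Randomisation protects the treatment comparison even if the age term is misspecified. For dichotomous outcomes the plan reports marginal relative risks, so the added covariate does not change the quantity estimated.

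**Conclusion.** The point holds as a minor matter of efficiency. The outcome regressions use age only as below or above 60 while age in years is on file. With near-normal age (mean about 58, SD about 12) and a linear effect, the split keeps about 63% of what age explains. The practical gain from adding age in years is about 0 to 1 power point for the primary outcome and 0 to 2 for EQ VAS. Where in those ranges it falls depends on how prognostic age is, which the document does not state; if age has little linear effect, the gain is nil. The sample size and the validity of the planned analysis are unaffected.

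**What to change.** Before unblinding, amend the Continuous, Ordinal and Dichotomous outcomes sections, and the matching sentence on the logistic model under Assessments of underlying statistical assumptions. State that the models adjust for the modified Fisher stratum, the age stratum and age in years as a continuous variable, as fixed effects, with site as random effect. Leave the strata unchanged for randomisation and for the van Elteren test.

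The cost is one phrase in the plan and one extra parameter per model. No new data are needed. Because the analysis is done under code, the change can be prespecified without knowledge of the allocation. If the sponsor prefers to keep the strata-only models, that is defensible, and a line saying so would close the point.

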### Trial interventions

The interventions have been described in detail elsewhere [9]. In brief, participants will be randomised to either (1) gradual weaning, which comprises a stepwise increase of resistance to outflow ending with complete closure of the EVD, or (2) prompt closure which involves direct closure of the EVD at time of randomisation. If weaning or closure is tolerated, the EVD is removed 24 and 48 h after closure, respectively, for gradual weaning and prompt closure. For gradual weaning, if the EVD resistance is decreased during the gradual weaning attempt, one additional identical attempt is initiated when the patient is clinically stable, i.e. when he/she fulfils the inclusion criteria again. The participants are thus allowed two attempts of gradual weaning and if both attempts fail, this is classified as a failure. For prompt closure, if the intervention is not tolerated, the EVD is reopened at the level from which closure was done. The participants are allowed one additional attempt of prompt closure of the EVD. If the participant fails two attempts of prompt closure, rescue intervention in the form of two attempts of gradual weaning (as described above) is allowed.

In case of discontinuation, the participant stays in the allocated intervention group, and all outcomes are collected at follow-up.

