**Exploratory outcomes**	
Functional outcome according to modified Rankin Scale (mRS) at 6 months (1–6 scale)	Ordinal
The remaining dimensions of EQ-5D-5L (mobility, self-care, usual activities, pain/discomfort, and anxiety/depression) at 6 months (1–5 levels)	Count
Glasgow Outcome Scale Extended (GOSE) at 6 months (1–8 scale)	Ordinal
Reason for failure of EVD cessation (ICP elevation, drop in GCS by 2 points or more, and/or clinical deterioration)	Count
GCS on discharge from the Neuro Intensive Care Unit and Neurosurgical department	Count
Length of stay in Neuro Intensive Care Unit	Count
Length of stay in hospital	Count

*aSAH* aneurysmal subarachnoid haemorrhage, *EVD* external ventricular drain, *GCS* Glasgow Coma Scale, *ICP* intracranial pressure, *SAE* serious adverse events, *VP-shunt* ventriculoperitoneal-shunt

Secondary outcomes are:

Number of serious adverse events (SAE) not including mortality and defined according to International Conference of Harmonization of Good Clinical Practice (ICH-GCP) within 6 months (count outcome)Health-related quality of life (EQ-5D-5L) at 6 months [11] with the primary assessment being self- assessment of own health (EQ VAS; 0 to 100 point scale) (continuous outcome)Fatigue Severity Scale (FSS) mean score at 6 months [12]

Exploratory outcomes are:

Functional outcome according to modified Rankin scale (mRS) at 6 months [13, 14] (1–6 scale) (ordinal outcome)The remaining dimensions of EQ-5D-5L (mobility, self-care, usual activities, pain/discomfort, and anxiety/depression) at 6 months [11] (1–5 levels) (count outcome)Glasgow Outcome Scale Extended (GOSE) at 6 months [15] (1–8 scale) (ordinal outcome)Reason for failure of EVD cessation (ICP elevation, drop in GCS by 2 points or more, and/or clinical deterioration)GCS on discharge from the Neuro Intensive Care Unit and Neurosurgical departmentLength of stay in Neuro Intensive Care UnitLength of stay in hospitalEach component of the primary outcome will be analysed as exploratory outcomesEach component of the composite outcome will be analysed as exploratory outcomes

VP-shunt implantation is the consequence of failed EVD discontinuation and as such is included in the composite endpoint. The explanatory outcomes cover among other the reasons for the EVD discontinuation to be deemed a failure, e.g. intracranial hypertension or clinical deterioration.

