### Sample size and power justification

#### Sample size estimation

Data from the only previous randomised clinical trial suggest a VP-shunt implantation proportion of 63% in patients with acute need of CSF diversion following aSAH [5]. The mortality following aSAH is commonly quoted to be 27% to 50%, while 5.8% of patients develop an EVD-related infection [2, 7]. Assuming an incidence of either of the three components of the composite primary outcome (VP-shunt implantation, all-cause mortality, or EVD-related infection) within 6 months of 80%, an *α* = 0.05 (two-sided), and a *β* = 0.20, 2 × 122 participants are required to detect a 20% relative risk reduction or increase calculated using R (R Core Team, Vienna, Austria)*.* For composite outcomes, one missing component will result in missingness in the composite outcome. Number and percent missing due to a missing component will be stated in the report or in a diagram to avoid biased result, e.g. from death alone.

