## Limitations

Since no correction for multiplicity will be applied to the secondary or exploratory outcomes, any significant findings must be interpreted with caution. We assess multiple outcomes, which increases the risk of false positive results (type I errors); any difference between the groups might be explained by random errors (‘play of chance’). Even with the objective assessment of the primary outcome, we cannot ensure that neither clinicians nor investigators can introduce unconscious bias. Finally, interim analyses were not included in the trial setup, which does not directly limit the statistical analyses, but the overall trial could have profited from this addition. Since all but 1 participant are included, it would not be sensible to carry out any interim analyses.

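### The primary outcome is not free from bias as the plan states, and because only the prompt-closure arm has rescue attempts, a lower rate there supports the regimen and not prompt closure alone

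*SAP article*

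**What the plan says.** **Attempts.** Under Trial interventions, the rule for the weaning arm is: "The participants are thus allowed two attempts of gradual weaning and if both attempts fail, this is classified as a failure". The prompt-closure arm has a first attempt and one further attempt, and then: "If the participant fails two attempts of prompt closure, rescue intervention in the form of two attempts of gradual weaning (as described above) is allowed". That is at most two attempts in one arm and four in the other, the last two using the comparator's technique.

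**Link to the primary outcome.** The composite is VP shunt, death from any cause or EVD-related infection within 6 months of ictus. On the shunt, the Outcomes section explains: "VP-shunt implantation is the consequence of failed EVD discontinuation and as such is included in the composite endpoint". Infection may be established by culture, by antibiotic treatment for EVD-related infection, or by both.

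**Blinding.** Under Randomisation and blinding, participants and clinicians are unblinded, and blinded assessors rate the composite. The section then says: "However, the primary outcome is an objective assessment not susceptible to bias". The Limitations section says: "we cannot ensure that neither clinicians nor investigators can introduce unconscious bias".

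**Framing.** The Introduction speaks of comparing regimens and strategies, and the primary analysis is by intention to treat.

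**The concern.** There are two separate issues.

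The first is a claim about bias that the design cannot support. Blinded assessment protects the classification of events that have already happened. It does not protect the decisions that create those events. Placing a shunt and starting antibiotics are decisions of clinicians who know the allocation, and each can make a participant a primary-outcome event.

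The second is what the treatment effect means. If a shunt follows failed cessation and one arm is allowed two further attempts, part of any reduction in shunts in that arm may come from the further attempts and not from closing the drain promptly. A reader told only that prompt closure was compared with gradual weaning could credit the whole difference to the technique. The same ambiguity affects the reason-for-failure outcome: this document says when failure is declared for weaning only, so failure could be recorded after two attempts in one arm and after four in the other.

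**Working it through.** **1. The plan's own figure.** The inputs are 80% in the weaning arm, a 20% relative reduction (0.80 × 0.80 = 64%), two-sided alpha 0.05 and power 80%. The plan concludes: "2 × 122 participants are required to detect a 20% relative risk reduction or increase". The arcsine formula gives exactly 122 per arm. The pooled normal formula gives 123, and power at 122 per arm is 79.9%. The sample size reproduces and is not in dispute.

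**2. The two statements on bias side by side.**

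| Component | Who decides that it happens | What a blinded assessor can do |
|---|---|---|
| VP shunt | Unblinded clinicians | Confirm that it was placed |
| Infection, antibiotic criterion | Unblinded clinicians | Confirm that treatment was given |
| Infection, culture criterion | Laboratory result | Confirm the result |
| Death | Not a decision of this kind | Confirm it |

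The statement under Randomisation and blinding is therefore too strong for the shunt and for the antibiotic criterion, and it conflicts with the Limitations section.

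**3. How much the extra attempts could contribute.** The inputs from Sample size estimation are a shunt proportion of 63% and a composite of 80%.

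Assumptions, none of them stated in the plan:
- the techniques are equally good, so 63% would be shunted after two attempts in either arm;
- every participant who fails prompt closure twice uses both rescue attempts;
- rescue spares a share *s* of those otherwise shunted;
- longer drainage adds no infections.

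The prompt-arm shunt proportion is then 0.63 × (1 − *s*). The composite depends on how the other events overlap with shunts:
- *No overlap:* other events add 0.80 − 0.63 = 0.17, so composite = 0.63(1 − *s*) + 0.17. For a given *s* this is the largest possible effect.
- *Independence:* 1 − *o* = 0.20/0.37 = 0.5405, where *o* is the probability of another event, so composite = 1 − [1 − 0.63(1 − *s*)] × 0.5405.

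Worked at *s* = 20%, shunts fall to 0.504. With no overlap the composite is 0.504 + 0.17 = 0.674, and RR = 0.674/0.80 = 0.84. Under independence it is 1 − 0.496 × 0.5405 = 0.7319, and RR = 0.7319/0.80 = 0.9149, or 0.91.

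| *s* | Composite, no overlap | RR | Chance of p < 0.05 | Composite, independent | RR | Chance of p < 0.05 |
|---|---|---|---|---|---|---|
| 10% | 73.7% | 0.92 | 21% | 76.6% | 0.96 | 9% |
| 20% | 67.4% | 0.84 | 61% | 73.2% | 0.91 | 24% |
| 30% | 61.1% | 0.76 | 90% | 69.8% | 0.87 | 45% |

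The chance of significance is the power of a two-sided comparison of proportions with 122 per arm.

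**4. Rescue share that reproduces the full design effect (64%).**
- *No overlap:* shunts = 0.64 − 0.17 = 0.47, so *s* = 1 − 0.47/0.63 = 25.4%.
- *Independence:* 1 − shunts = 0.36/0.5405 = 0.666, so shunts = 0.334 and *s* = 1 − 0.334/0.63 = 47%.

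If each of the two rescue attempts succeeds with probability *q*, then 1 − *s* = (1 − *q*)². This gives *q* = 1 − √0.746 = 13.6% with no overlap and *q* = 1 − √0.530 = 27% under independence.

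**The case against.** The strongest reply is that the number of attempts is part of what was randomised. It is not a measurement bias and does not by itself refute a sentence about outcome assessment. The Introduction already speaks of strategies and regimens, the rescue is described as part of the prompt-closure pathway, and intention to treat is the matching analysis. All of this stands, which is why the two issues are kept apart here and the primary comparison is not called invalid.

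The plan also goes some way towards the question. It analyses each component separately, plans a per-protocol analysis, and examines first-attempt success in the first embedded study of Table 4. None of these equalises the attempts or sets the rescue aside. The components carry the same asymmetry, the per-protocol text does not say how rescued participants are classed, and the embedded study stops at the first attempt and concerns predictors. The point at which failure is declared in the prompt arm may be fixed in the protocol, which this document cites for detail, so no error is alleged there.

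A reader might infer that about 10.6% success per rescue attempt is enough to produce the effect for which the trial is powered, since (1 − 0.106)² = 0.80. The documents do not support this. That figure is a 20% cut in shunts, whereas the trial is powered on the composite, where it corresponds to the *s* = 20% row above (RR 0.84 or 0.91).

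**Conclusion.** The sentence that the primary outcome is not susceptible to bias is wrong as written and must be reconciled with the Limitations section. The intention-to-treat result is a valid comparison of prompt closure with weaning as rescue against weaning, but a lower rate in the prompt arm cannot be assigned to prompt closure alone.

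The size is uncertain. Under the stated assumptions, a rescue share of 20% gives a composite RR of 0.84 to 0.91 with no difference between the techniques. The full design effect needs about 25% to 47% rescued, or 13.6% to 27% success per attempt. The documents give no rescue rate, the rescue is allowed and not required, and extra infections from longer drainage could offset the advantage.

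A reader might go further and infer that the trial's result is uninterpretable, or that the blinded abstracts will over-claim. Neither follows. The point weakens only a lower rate in the prompt arm; a result favouring weaning would have arisen despite fewer attempts. The abstracts were still to be written when the plan was published.

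**What to change.** No change to care is proposed, and no view is taken on which attempt or rescue rule is right.

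1. Delete or qualify the sentence on susceptibility to bias under Randomisation and blinding so that it agrees with Limitations. Add a sensitivity analysis of the composite that counts only culture-positive infection. This reduces the dependence on clinicians' decisions but does not remove it, because shunting is still a clinical decision.
2. State that the primary contrast is between regimens, with weaning as rescue in the prompt-closure arm, and word both blinded abstracts in those terms.
3. Prespecify a supportive analysis of failure after the first two allocated attempts in each arm, with any rescue weaning counted as failure, using the planned mixed-effects logistic model and RR. Classify reason for failure at that same point in both arms.

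The cost is some SAP wording, two supplementary analyses (the second needs attempt-level records) and a narrower headline claim. The plan puts the end of follow-up at December 2024 and the analysis after trial completion under coded groups. The additions count as prespecified only if they are fixed before unblinding; after that they would be post hoc.
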